**Fig. 1 Fig1:**
[figure not shown]
Flowchart of the FORCE trial. Abbreviations: M1–4, measurement 1 till 4. LAR, low anterior resection

Patients who decline the request for participation will be asked to fill out the DeFeC questionnaire (with Wexner score included) and LARS score only one time. These patients will sign a separate informed consent form for this step (Additional file 2). Study participation for these patients will stop directly after finishing these questionnaires. By means of this questionnaire, a valid statement can be made about the potential selection bias for participation that is based on the amount of complaints.

Patients from the control group who would like to undergo PFR will be given the opportunity to undergo this treatment after finishing measurement 3 (M3). These patients will undergo an identical PFR program as the patients that are initially randomized to this intervention and will be asked to fill in another questionnaire (similar to M2/M3) after their treatment. This might provide useful information about whether the timing of PFR is of influence on the results.

This study protocol is in accordance with the 2013 Standard Protocol Items: Recommendations for Interventional Trials (SPIRIT) Statement [17]. The checklist can be found in Additional file 3. The schedule of enrollment, interventions, and assessments is shown in Table 1.

**Table 1 Tab1:** The schedule of enrollment, interventions, and assessments (according to the SPIRIT statement 2013)

TIME POINT		STUDY PERIOD				
	Enrollment	Allocation^a^	Post-allocation			Close-out
	October 2017 – December 2019	0	t_1_^b^	t_2_^b^	t_3_^b^	December 2019 – June 2020.
ENROLLMENT:						
Eligibility screen	X					
Informed consent	X					
Randomization and allocation		X				
INTERVENTIONS:						
Pelvic Floor Rehabilitation			X			
Control group			X			
ASSESSMENTS:						
Questionnaires to assess study outcomes			X	X	X	
Statistical analysis						X

^a^Allocation of the intervention/control group takes place 3 months after index surgery without temporary stoma construction or 6 weeks after stoma reversal if initial surgery included stoma construction. Measurement t1 will always take place before randomization/allocation

^b^*t1* measurement before randomization, *t2* primary endpoint (12 weeks after control/intervention period), *t3* one year follow-up

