### Flow of the FORCE trial

After surgery, eligible patients will be randomized for either a standardized pelvic floor rehabilitation (PFR) program or standard treatment, which is defined as current daily practice. Blinding for PFR is not possible. Randomization and data collection will be performed by the coordinating investigator. In concordance with the study flowchart (Fig. 1), these steps will be followed:
After giving informed consent, eligible patients will be included in the FORCE trial. In the beginning of the inclusion period, this inclusion was supposed to occur preoperatively with a baseline measurement before surgery as well (measurement 1, M1). Since this preoperative inclusion led to reduced numbers of inclusion due to an overload of information, postoperative inclusion was allowed as well.Questionnaires will be administered 3 months after LAR (measurement 2, M2) to patients without a temporary stoma. Based on the current reports, approximately 70% of patients undergoing LAR also receive a temporary stoma [16]. In these cases, the questionnaires will be administered 6 weeks after stoma closure (measurement 2, M2).Randomization will take place after completing the M2 questionnaires. Patients will then undergo either standard treatment or a standardized PFR program that includes the standard treatment for 3 months (12 sessions, once a week).After finishing the PFR program or 12 weeks of participation in the control group, questionnaires will be send again (measurement 3, M3, primary endpoint).Long-term follow-up will be completed at 1 year after bowel continuity (measurement 4, M4).

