### Randomization, stratification, and blinding

#### Randomization and stratification

Randomization will be performed 3 months after the LAR in patients without stoma construction, and in case of a temporary stoma, 6 weeks after stoma closure. The coordinating investigator will conduct the randomization procedure, using Castor EDC (www.castoredc.com). Stratification will be done in variable blocks. It will be stratified for gender and radiation because of frequent sphincter function impairment due to birth trauma in women and the association between radiation and sphincter and bowel dysfunction. The coordinating investigator will be responsible for communication with the pelvic floor specialized physiotherapists and will inform them about referral and the allocated intervention.

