## Trial status

This is protocol version number 18 (approved 19 September 2019) of an ongoing trial. Recruitment started October 2017 and is expected to finish January 2020. Patient recruitment has not been completed at the time of submission of this article.

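### Table 1 ends close-out, and with it the statistical analysis, in June 2020, before the last 1-year measurements (M4) fall due

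*Protocol article*

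**What the plan says.** All references are to the protocol article.

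- **Table 1 (under Flow of the FORCE trial)** dates enrolment "October 2017 – December 2019" and close-out "December 2019 – June 2020". Statistical analysis is marked only under close-out. The third questionnaire round, t3, is explained as "one year follow-up" and sits in a post-allocation column ahead of close-out.
- **Trial status** gives a different end of recruitment: "Recruitment started October 2017 and is expected to finish January 2020".
- **Flow of the FORCE trial** fixes the last measurement: "Long-term follow-up will be completed at 1 year after bowel continuity (measurement 4, M4".
- **Randomization and stratification** fixes the starting point: "Randomization will be performed 3 months after the LAR in patients without stoma construction". The remaining patients have a different time point, which the same sentence gives as "in case of a temporary stoma, 6 weeks after stoma closure".
- **Primary outcome** gives M4 a planned analysis. It is to show whether results last, using the same ANCOVA as at M3, run with and without control patients who later took up pelvic floor rehabilitation.

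The article nowhere limits the June 2020 date to the primary endpoint, and it gives no later date for M4.

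**The concern.** The three calendar statements cannot all hold. A patient randomised in the last months of enrolment cannot reach the 1-year measurement before close-out ends, yet Table 1 allows for no analysis after that date.

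M4 is at stake. It is the last scheduled measurement and the one meant to show durability. The economic evaluation observes 6 months and supposes that the effect lasts 5 years. M4 is already weakened by control patients crossing over after M3 and by an assumed 50% withdrawal. Losing the latest patients as well, only because of a date in a table, would be avoidable.

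**Working it through.** **Inputs from the article.** Enrolment starts October 2017 and ends December 2019 (Table 1) or January 2020 (Trial status). Close-out ends June 2020. M4 is 12 months after continuity. Randomisation is 3 months after LAR without a stoma, or 6 weeks (1.5 months) after stoma closure. On the stoma share, the Flow section says "approximately 70% of patients undergoing LAR also receive a temporary stoma". The planned number randomised is 128.

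**Assumptions not in the article.** Accrual is uniform, the enrolment date is the randomisation date, 70% of randomised patients had a stoma, and the cut-off is 30 June 2020. Continuity is dated from LAR (no stoma) or from closure (stoma).

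**Step 1: time from randomisation to M4.**
- No stoma: 12 − 3 = 9 months.
- Stoma: 12 − 1.5 = 10.5 months.

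**Step 2: date of the last M4.** Count months from 1 October 2017, so that the end of December 2019 is 27, the end of January 2020 is 28 and the end of June 2020 is 33.

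| Enrolment ends | No stoma | Stoma |
|---|---|---|
| December 2019 | 27 + 9 = 36, end of September 2020 | 27 + 10.5 = 37.5, mid-November 2020 |
| January 2020 | 28 + 9 = 37, end of October 2020 | 28 + 10.5 = 38.5, mid-December 2020 |

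The overrun is 36 − 33 = 3 months to 38.5 − 33 = 5.5 months, before any time for analysis. This step needs no accrual assumption: even a no-stoma patient randomised on 1 December 2019 reaches M4 only about 1 September 2020.

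**Step 3: share of patients with M4 after the cut-off.** M4 by month 33 requires randomisation by month 33 − 9 = 24 (end of September 2019, no stoma) or 33 − 10.5 = 22.5 (mid-August 2019, stoma). With T months of uniform accrual, the late share is [T − (33 − lag)]/T.
- T = 27: 3/27 = 11.1% and 4.5/27 = 16.7%. Weighted: 0.3 × 11.1 + 0.7 × 16.7 = 15.0%, or 19 of 128.
- T = 28: 4/28 = 14.3% and 5.5/28 = 19.6%. Weighted: 0.3 × 14.3 + 0.7 × 19.6 = 18.0%, or 23 of 128.

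**Step 4: varying the dates.**
- Enrolment stops on 1 December 2019 (T = 26): 2/26 = 7.7% and 3.5/26 = 13.5%, weighted 11.7%.
- Cut-off at 1 June 2020 (month 32): 18.7% (T = 27) and 21.6% (T = 28).
- t3 read as 1 year after allocation: 6/27 = 22.2% and 7/28 = 25.0%.

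The range is about 12% to 25%.

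**Step 5: cost in precision.** If the loss falls evenly on both arms, the M4 confidence interval widens by 1/√(1 − share). That is 1/√0.85 = 1.08 to 1/√0.82 = 1.10 for the central figures, and 1/√0.883 = 1.06 to 1/√0.75 = 1.15 over the range.

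**Step 6: the primary endpoint.** With M3 about 3 months after randomisation, as the Flow section places it, the last M3 is at month 27 + 3 = 30 (end of March 2020) or 28 + 3 = 31 (end of April 2020). Both fall before June 2020.

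**The case against.** The strongest reply is that June 2020 is only a projected date. The Flow section still requires M4 for everyone, the abstract promises 1-year follow-up, and nothing calls June 2020 a data cut-off or excludes later questionnaires. The calendar is also coarse: close-out opens in the month enrolment ends, before the last patients can reach M3. A team following the Flow section would simply collect M4 and analyse it later. This stands in part. A reader might infer that M4 will be missing for late patients. The article supports that only if the Table 1 calendar governs.

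A reader might also infer bias, because inclusion moved from preoperative to postoperative and the late patients could therefore differ. The article does not date that change, and it places preoperative inclusion at the beginning of the inclusion period. Nothing shows that patients randomised in the last 3 to 5.5 months differ from most of those before them. A calendar cut-off also applies to both arms alike.

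The percentage is open to challenge as well. The article reports serious difficulty with enrolment followed by a change of recruitment method, which sits badly with uniform accrual. Later-weighted accrual would raise the share.

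Finally, it would be too strong to call the primary endpoint safe without condition. Table 1 puts screening and consent under Enrollment and randomisation in a separate, undated column. If the dates refer to consent, a patient who consents before stoma closure could be randomised well after January 2020, and both M3 and M4 would move later.

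None of this removes the conflict between the stated dates. The article itself states them, so it is not a detail left to a fuller document.

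**Conclusion.** The point holds as an inconsistency between the Table 1 calendar and the follow-up schedule, whatever the accrual pattern. The last M4 falls 3 to 5.5 months after the end of close-out, and more if enrolment means consent. If the Table 1 calendar governs, the M4 ANCOVA loses about 15% to 18% of randomised patients under the listed assumptions, and about 12% to 25% when the dates are varied. These shares are not figures from the article and should be quoted only with their assumptions.

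The consequence is lost precision and coverage of the latest patients at M4. No between-arm bias is shown. The primary analysis at M3 fits the calendar provided that the enrolment dates refer to randomisation. The correction is worth making because it protects a planned analysis, but it does not touch the sample size, the allocation or the primary comparison.

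**What to change.** 1. Give one enrolment end date in Table 1 and Trial status, and say whether it refers to consent or randomisation.
2. State that the M3 primary analysis runs after the last patient's M3.
3. In Table 1, move the end of M4 collection, the M4 analysis and close-out to after the last randomised patient's M4. On the present dates this is not before mid-November 2020, or mid-December 2020 with recruitment to January 2020. It is later still if those dates refer to consent.

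The cost is several more months of mostly online questionnaires and a later final report. No extra patients are needed.

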### Recruitment and informed consent

The Committee on Research Involving Human Subjects Arnhem-Nijmegen approved the FORCE trial. All patients with proven colorectal cancer will be treated according to standard surgical protocols. Patients who meet the inclusion/exclusion criteria will be selected and asked for participation for this study by their own surgeon. The surgeon will inform the patients by handing out the patient information and will ask for permission to inform the coordinating investigator about his/her possible participation. This step will be noted in the electronic health records. After a reasonable time (2 weeks), the coordinating researcher will call the patient to answer potential questions. The patients will have 2 weeks to consider before renewed contact is made. When patients decide to participate, they will sign the Informed Consent and send it to the coordinating investigator at Radboud University Medical Center (Radboudumc). The coordinating investigator will be responsible for storing the signed Informed Consent in the Trial Master File at Radboudumc and in the investigator site files at the participating centers. On the consent form, participants will be asked if they agree to the use of their data. Participants will also be asked for permission for the research team to share data with the regulatory authorities, where relevant.

### Randomization, stratification, and blinding

#### Randomization and stratification

Randomization will be performed 3 months after the LAR in patients without stoma construction, and in case of a temporary stoma, 6 weeks after stoma closure. The coordinating investigator will conduct the randomization procedure, using Castor EDC (www.castoredc.com). Stratification will be done in variable blocks. It will be stratified for gender and radiation because of frequent sphincter function impairment due to birth trauma in women and the association between radiation and sphincter and bowel dysfunction. The coordinating investigator will be responsible for communication with the pelvic floor specialized physiotherapists and will inform them about referral and the allocated intervention.

#### Blinding

The physiotherapists will be informed about the pre- and postoperative medical history of the patient. Surgeons and physiotherapists are blinded in terms of outcomes of questionnaires taken before the start of PFR (measurement M2, Fig. 1). Complete blinding of the allocated intervention for patients and the participating physiotherapists is impossible. Unblinding will not occur, since the design is open label. The coordinating investigator, who will also be involved in data analysis, is not blinded for the allocation since he will inform the physiotherapists about referral and the allocated intervention. Additional data analysists will be blinded for allocation.

### Data analysis and statistics

#### Primary outcome

The primary outcome is based on the Wexner score. The dependent variable is the severity of FI measured by this score. The independent variable is the intervention or the standard treatment. The difference between the intervention and control group will be analyzed by an analysis of covariance (ANCOVA), with the baseline measurement as covariate. This test is preferred over the T-test since this analysis reduces the within-group error variance. Therefore, the precision of the treatment estimate is increased, and the length of the confidence interval is reduced [18]. The M3 measurement will be valid as the primary outcome. The M4 measurement, which is used to assess sustainability of results, will be influenced by the patients of the control group who will choose to undergo PFR after finishing their primary endpoint measurements (after 3 months of standard treatment, i.e., in case of severe FI). For statistical analysis, the effect between the intervention group and control group will be evaluated with and without this group to measure the influence of this group on the M4 measurement. The same analysis of covariance (ANCOVA) will be used.

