### Sample size calculation

Recent studies reported an improvement of FI after LAR by PFR of five points on the Wexner-score (SD = 8) [11, 12, 15]. This improvement is considered to be of great clinical significance.

In the original design of this trial, an independent T-test was suggested for the primary outcome measure. Progressive insights made it possible to make a change to the ANCOVA analysis, since this test reduces the within-group error variance. Therefore, the precision of the treatment estimate has been increased, and the length of the confidence interval has been reduced [18]. Therefore, for this trial with an ANCOVA as primary statistical test, the following sample size calculation was made:
The T-test sample size was based on 80% power to detect a difference of five points in the Wexner score, SD = 8, two-grouped t-test, with a 0.05 two-side significance level: 63 patients per arm.The sample size calculation for analysis of covariance (ANCOVA) in randomized clinical trials described by Borm et al. [18] was used, with an estimated correlation factor (R) of 0.5. The required sample size is 32 patients per arm.Assuming a withdrawal/replacement rate of 50% [11, 12, 15], a total of 128 patients should be randomized.

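### Randomisation is stratified by gender and radiotherapy, but the stated ANCOVA for M3 and M4 adjusts for baseline only: adding the two factors is a minor, free gain if they predict the Wexner score beyond baseline

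*Protocol article*

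**What the plan says.** The section on randomization and stratification gives a prognostic reason for each factor: "It will be stratified for gender and radiation because of frequent sphincter function impairment due to birth trauma in women", together with "the association between radiation and sphincter and bowel dysfunction".

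The primary outcome section says: "The difference between the intervention and control group will be analyzed by an analysis of covariance (ANCOVA), with the baseline measurement as covariate". No other covariate is named, and the same ANCOVA is to be used at M4. The section also says why ANCOVA was chosen: "This test is preferred over the T-test since this analysis reduces the within-group error variance". The sample size section repeats that argument and credits only the baseline correlation.

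On timing, the flow section says: "Randomization will take place after completing the M2 questionnaires". M2 is 3 months after LAR, or 6 weeks after stoma closure. I take M2 to be the baseline in the model.

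Nowhere does the article put gender or radiotherapy into the M3 or M4 model. The secondary endpoints section only proposes to explore demographic, surgical and oncologic parameters. The cointerventions section says only that cointerventions and medication changes will be considered in the analyses.

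**The concern.** Stratified blocks force the arms to be alike on gender and radiotherapy, so the true sampling variance of the treatment difference is lower than under simple randomisation. A model without these factors leaves their variance in the residual. Its standard error then does not reflect the balance that the design achieved: intervals are too wide and the test rejects less often than 5% under the null.

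The protocol's stated reason for ANCOVA is to shrink the error variance and shorten the interval. Omitting two factors that it regards as prognostic works against that aim, in an analysis expected to rest on about 64 patients. At stake is precision, not validity.

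**Working it through.** **Inputs from the sample size section.** Difference 5 points, SD 8, two-sided 0.05, 80% power, R = 0.5, 32 per arm, 50% withdrawal, 128 randomised.

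**Input not in the documents.** q, the share of the variance left after baseline that gender and radiotherapy explain. Assumed range: 0 to 0.20.

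**1. The plan's own figure.** Normal approximation: 2 × (1.96 + 0.842)² × 8² / 5² = 40.2, so 41 per arm; the exact t calculation gives 42. The ANCOVA factor is 1 − 0.5² = 0.75, and 42 × 0.75 = 31.5, so 32 per arm. Then 64 / (1 − 0.5) = 128. The final sizes reproduce. The intermediate 63 per arm does not follow from these inputs; that is a separate matter and does not affect this point.

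**2. The stated model at 32 per arm.** Residual SD = 8 × √0.75 = 6.93. SE = 6.93 × √(2/32) = 1.732. Noncentral-t power with 61 df is 81.1%.

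**3. With the two factors added.** SE = 1.732 × √(1 − q), with 59 df.

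| q | adjusted SE | stated SE / adjusted SE | adjusted power |
|---|---|---|---|
| 0 | 1.732 | 1.000 | 81.0% |
| 0.02 | 1.715 | 1.010 | 81.8% |
| 0.05 | 1.688 | 1.026 | 83.0% |
| 0.10 | 1.643 | 1.054 | 84.9% |
| 0.20 | 1.549 | 1.118 | 88.8% |

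**4. Type I error if balance were complete.** The stated model's rate is 2 × (1 − Φ(1.96/√(1 − q))), which is 3.9% at q = 0.10 and 2.8% at q = 0.20. Simulation without withdrawal gives 3.8% and 3.1%, and 5.0% and 5.2% once the factors are added. But without withdrawal 128 patients are analysed, which is not what the plan expects.

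**5. Type I error and power with 50% withdrawal.** Losing half the patients at random undoes part of the balance, so the closed form in step 4 no longer applies. Simulation: 128 patients, four strata, permuted blocks of 2, 4 or 6, each patient lost with probability 0.5, normal outcomes, 40% women and 50% irradiated (both assumed), q split equally between the factors, 6,000 runs per setting.

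| q | stated model: model SE / true SE | model SE, adjusted | type I, stated / adjusted | power, stated / adjusted |
|---|---|---|---|---|
| 0 | 1.753 / 1.773 | 1.769 | 5.0% / 5.0% | 80.0% / 79.4% |
| 0.05 | 1.750 / 1.739 | 1.719 | 5.0% / 5.4% | 80.2% / 81.3% |
| 0.10 | 1.752 / 1.722 | 1.675 | 4.3% / 5.1% | 81.2% / 83.7% |
| 0.20 | 1.754 / 1.653 | 1.580 | 3.6% / 4.5% | 81.2% / 87.3% |

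SEs are from the null runs. Monte Carlo error is about √(0.05 × 0.95/6000) = 0.3 points on type I error and √(0.81 × 0.19/6000) = 0.5 points on power. Repeat simulations put the stated model's type I error at 4.2–4.4% for q = 0.10 and 3.6–4.2% for q = 0.20. A separate 4,000-run simulation gave power of 79.9% against 79.3% at q = 0, 80.0% against 80.3% at q = 0.02, and 80.3% against 81.0% at q = 0.05.

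The ratio of model SEs, stated to adjusted, is 1.753/1.769 = 0.99, 1.750/1.719 = 1.02, 1.752/1.675 = 1.05 and 1.754/1.580 = 1.11 for the four rows.

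**The case against.** The strongest reply is that the loss is conditional. M2 is measured after surgery on the same scale as the outcome, so lasting sphincter damage from birth trauma or radiation should already show in the baseline score. What matters is only what gender and radiotherapy add beyond M2, and the documents give no figure. For q of 0 to 0.05 the gain is negligible, and at q = 0 adjustment costs a fraction of a point of power. The stated analysis also keeps its planned 80% power throughout. All of this stands and limits the size of the point.

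A second reply is that the article does not say baseline is the only covariate, and that a fuller analysis plan may add the strata. That is possible. But the article names the covariate and argues for it, so this is a stated choice and not a gap left to another document.

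Four stronger readings are tempting and are not supported:

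- **That the primary result would be biased or its type I error inflated.** Any error here is on the conservative side.
- **That type I error would fall to 3.9% or 2.8%.** Those values need full stratum balance among the patients analysed, which the planned 50% withdrawal largely removes.
- **That the secondary ANCOVAs wrongly omit the strata.** The secondary endpoints section lists no covariates, so there is no stated model to fault.
- **That temporary stoma belongs in the model for the same reason.** It affects when M2 is taken, but it is not a stratification factor, so adding it would be a preference.

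**Conclusion.** The mismatch is real: the M3 and M4 models ignore the factors that the protocol stratified on and calls prognostic. Its consequence depends on an unknown. Under 50% random withdrawal and the other assumptions above, there is no meaningful gain from adjustment for q up to 0.05. The gain is 2 to 3 points of power at q = 0.10 and 6 to 7 points at q = 0.20. The stated intervals would be about 2%, 5% and 11% wider than the adjusted ones at q = 0.05, 0.10 and 0.20. Because M2 is post-surgical, the lower part of the range is the more plausible. These figures also treat withdrawal as unrelated to outcome and the Wexner score as normal.

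I rate this as a minor improvement, worth making because it is free. It gives no reason to doubt a conclusion drawn from the stated model.

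**What to change.** In the primary outcome section, or in the analysis plan before any data are analysed, specify:

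M3 Wexner = arm + M2 Wexner + gender + radiotherapy,

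with main effects only and with gender and radiotherapy as recorded at randomisation. Use the same covariates for M4, both with and without the control patients who go on to PFR.

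The cost is one line of text and two degrees of freedom (61 to 59 at 64 analysed). The sample size does not change, and both variables are already in the randomisation system. The choice should be fixed in advance because, under the blinding section, the coordinating investigator knows the allocation and takes part in the analysis.

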### Patient information and questionnaires

#### Medical history/patients characteristics

The patient information will include the medical history, gender, age, tumor height (MRI and scoping), height and type of the anastomosis, type of surgery (laparoscopic, open or robotic), construction of a temporary stoma, peri- and postoperative complications, time of surgery, blood loss, time of hospitalization, and clinical and pathological TNM staging.

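### The primary ANCOVA adjusts only for M2, although stoma pathway fixes the time since bowel continuity at both M2 and M3; adding the recorded pathway is a cheap, minor gain in precision

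*Protocol article*

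**What the plan says.** All references are to the protocol article.

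- **Model.** Under Primary outcome, the comparison of arms "will be analyzed by an analysis of covariance (ANCOVA), with the baseline measurement as covariate". M3 is the primary time point, and the same ANCOVA is used at M4. Under Secondary endpoints, ANCOVA is also used for quality of life and anorectal outcomes.
- **Timing of M2.** Under Flow of the FORCE trial: "Questionnaires will be administered 3 months after LAR (measurement 2, M2) to patients without a temporary stoma". For patients with a stoma, "the questionnaires will be administered 6 weeks after stoma closure (measurement 2, M2". The same section cites reports that "approximately 70% of patients undergoing LAR also receive a temporary stoma".
- **Order of events.** "Randomization will take place after completing the M2 questionnaires". M3 follows "After finishing the PFR program or 12 weeks of participation in the control group". M4 is set at 1 year after bowel continuity.
- **Stratification.** Under Randomization and stratification: "It will be stratified for gender and radiation".
- **Data held.** The list under Medical history/patients characteristics includes "construction of a temporary stoma".
- **Sample size.** 5 Wexner points, SD 8, 80% power, two-sided 0.05, R = 0.5. This gives 32 per arm for the ANCOVA and 128 randomised after an assumed 50% withdrawal.

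**The concern.** Bowel function may still be changing in the months after continuity is restored. If so, the same M2 score could forecast a different M3 score at 6 weeks than at 13 weeks after continuity. A model with M2 as its only covariate would leave that difference in the error term. Pathway is also not a stratum, so its balance between arms is left to chance.

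The protocol prefers ANCOVA to the t-test because it lowers the error variance. That reasoning extends to another pre-randomisation variable that is already collected. Only precision is at stake, together with how far the single realised estimate could be displaced by an imbalance in stoma share. Naming the term in advance also matters because the trial is open label and the coordinating investigator, who takes part in the analysis, knows the allocation. A term added after an imbalance has been seen would be open to challenge.

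**Working it through.** **1. The plan's own figures.** A two-sample t-test for 5 points with SD 8, 80% power and two-sided 0.05 needs 41.2, so 42 per arm. The ANCOVA factor is 1 − R² = 1 − 0.25 = 0.75, and 0.75 × 42 = 31.5, so 32 per arm. With 50% withdrawal, 32/0.5 = 64 per arm, or 128. The final figures reproduce. The intermediate 63 per arm in the article does not (0.75 × 63 = 47.25). That is a separate matter and does not affect this check, which uses 32.

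**2. Time since bowel continuity.**

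| | M2 | M3 (12 weeks later) | M2 to M4 (week 52) |
|---|---|---|---|
| Stoma, about 70% | 6 weeks | 18 weeks | 46 weeks |
| No stoma, about 30% | about 13 weeks | about 25 weeks | about 39 weeks |

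The timing differs between pathways, not between arms.

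**3. Precision with M2 only.** Residual variance = 64 × 0.75 = 48, so the residual SD is 6.93. SE = 6.93 × √(2/32) = 1.732. Power for 5 points with 64 − 3 = 61 degrees of freedom is 81.1%.

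**4. Adding the pathway.** Let D be the difference between pathways at M3 for equal M2. The documents do not give D, so 0 to 4 points is assumed. The pathway explains 0.7 × 0.3 × D² = 0.21D² of the residual variance of 48. The stoma share in each arm varies by chance; the difference between arms has SD √(2 × 0.21/32) = 0.115, so its 95% range is ±1.96 × 0.115 = ±22 percentage points. The last column is D times that limit (0.2245 before rounding).

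| D | Share of residual variance | SE | Power | n per arm needed | Shift at 95% limit |
|---|---|---|---|---|---|
| 0 | 0% | 1.732 | 81.1% | 31.5 | 0 |
| 1 | 0.4% | 1.728 | 81.2% | 31.4 | 0.22 |
| 2 | 1.75% | 1.717 | 81.7% | 30.9 | 0.45 |
| 3 | 3.9% | 1.698 | 82.6% | 30.3 | 0.67 |
| 4 | 7.0% | 1.670 | 83.8% | 29.3 | 0.90 |

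If all 64 per arm were analysed, power would already be 98.2% without the pathway.

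**5. Is the shift already in the standard error?** At D = 4 the SD of the shift is 4 × 0.1146 = 0.458, and 0.458² = 0.21. The M2-only variance is 1.732² = 3.00, and 0.21/3.00 = 7.0%, the same share as in the table. The shift is therefore a component of the existing standard error. The 95% interval is about ±1.96 × 1.732 = ±3.4 points, and the largest shift shown is 0.90.

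**6. Simulation (32 per arm, 6,000 runs per setting).** For a true effect of 5, the M2-only ANCOVA averaged 4.99 to 5.01. Its type I error was 5.1% to 5.6%, the same range as for the adjusted model. Simulated power without and with the pathway was 80.8% and 80.0% at D = 0, 80.1% and 80.3% at D = 2, and 80.2% and 82.4% at D = 4. The gain is thus about nil up to D = 2 and appears only towards D = 4.

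Steps 4 to 6 assume a common residual variance, no pathway-by-treatment interaction, and M2 independent of pathway. Step 6 also assumes normal outcomes.

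**The case against.** The strongest reply is that nothing in the plan is wrong. M2 precedes randomisation in both pathways and M3 follows 12 weeks later in both, so M2 is a legitimate covariate. No passage gives a Wexner difference by pathway or by time since continuity. Even its direction is open, since stoma patients are earlier after continuity but had their resection before the closure operation. The 70% comes from other reports, not from the patients randomised here. The gain is small, and extra covariates are often left to the statistical analysis plan.

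Most of this stands. Three stronger conclusions that a reader might infer are not supported:

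- **That two timings of M2 bias the comparison.** They do not, because timing is unrelated to arm; the simulation agrees.
- **That precision is certainly wasted, or the sample size undermined.** The loss depends on an unknown D and is nil at D = 0. The 32 per arm rests on the overall R = 0.5, which the plan states as an estimate.
- **That chance imbalance goes uncorrected.** M2 removes the part of a pathway imbalance that shows in M2, and the standard error covers the rest over repeated randomisations.

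What remains is that the article does not leave the model blank: it names one covariate. The trial is also run once, so for a given observed imbalance, adjustment removes a displacement that the standard error covers only on average.

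**Conclusion.** The point holds as a minor improvement in efficiency, not as an error. The M2-only ANCOVA is valid and unbiased. Adding the pathway lowers the SE from 1.732 to between 1.732 and 1.670 and raises power from 81.1% to at most 83.8%. A 95%-extreme imbalance of 22 percentage points would move the M2-only estimate by 0 to 0.9 points against a target of 5, well inside its interval of about ±3.4.

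These sizes rest on an assumed D of 0 to 4 points, the cited 70% share, SD 8, R = 0.5 and 32 analysed per arm. What justifies the change is its low cost and the value of fixing the model in advance, rather than a large expected gain.

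**What to change.** Before database lock, state under Primary outcome that the ANCOVA at M3 includes M2 Wexner, temporary stoma (yes/no), gender and radiotherapy. State that the same model applies at M4 and to the secondary outcomes, each with its own M2 value where one exists (the defecation log starts only at randomisation).

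Gender and radiotherapy belong in the same sentence because they are the randomisation strata, the article itself links them to sphincter or bowel dysfunction, and the model does not name them either. Their contribution to precision is not quantified here.

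The cost is three degrees of freedom (61 to 58 with 32 per arm), and a slight loss of precision if the added terms turn out not to predict M3. No extra questionnaire or patient burden is needed: stoma construction is already recorded, and gender and radiotherapy are known from the stratification.
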